### Randomization and masking

All subjects were assigned into the two groups (described in the Study Design section) at a 1:1 ratio using covariate-adaptive randomization [33]. A scheduled randomization was generated and children were randomly assigned by Study Manager (ESSILOR R&D). The investigators cannot accessthe randomization list.

According to the scope of responsibilities, the examiners are either masked or unmasked. The masked examiners are responsible for subjective refraction, cycloplegic autorefraction, axial length, corneal thickness, anterior chamber depth measurements and assessing visual acuity with the study equipment. The unmasked examiners are in charge of dispensing and documenting adverse events.

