### Study participants

A total of 100 children were recruited from the hospital into this study between January and March 2019. The inclusion criteria were best-corrected visual acuity equal to or better than 1.0, age between 8 and 13 years inclusive, spherical equivalent of cycloplegic autorefraction between -0.75 D to -4.75 D in each eye, astigmatism no more than 1.50 D, anisometropia no more than 1.00 D, and absence of strabismus. Subjects with a history of ocular or systemic disease, history of wearing PALs, or prior myopia control treatment were excluded from participation in the study.

The study was designed to achieve 80% power to detect a minimum difference of 0.27 D with an SD of 0.37 D at 6 months at a 5% level of significance. Using an online sample size calculator by the Clinical & Translational Science Institute33, the theoretical sample size was 42 with a 1:1 sample ratio in each group. Allowing a maximum drop-out rate of 15%, the number to be recruited for each group was estimated to be 50.

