### Main outcome measures

There are two main outcome measures: the axial length (AL) and the spherical equivalent (SER) of cycloplegic autorefraction. The AL is measured using an optical low-coherence reflectometry device (Lenstar LS900; Haag-Streit, Koeniz, Switzerland). Five measurements were taken, and the average value per eye was used for data analysis. The refraction is measured by closed-field autorefractors (Topcon KR-800 and Topcon 8900). The measurement was taken ten times on each eye and the mode of the sphere, cylinder, and axis per eye is recorded for data analysis. The SER is calculated as sphere + 0.5 × cylinder. The SER is taken only at baseline, the fifth visit and the last visit to minimize cycloplegia during the study.

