#### Prospective data analyses

The changes in spherical equivalent cycloplegic autorefractiveerror and AL between the follow-up and baseline data will be used to evaluate myopia progression. Myopia progression and axial elongation will be compared between the SAL lenses and the single vision lenses using independent-samplet test. A multivariate regression model will be used to evaluate the relationships between variables such as age, gender, baseline myopia, parental myopia, NPC and phoria level, and myopia progression.

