## Discussion

Although numerous interventions are currently available to slow myopia progression, it still be beneficialfor young children to develop effective and safe strategies for myopic retardation. Spectacle lenses with contiguous aspherical lenslets may be an interesting option. At present, there are few reports on the myopia control effect of these lenses. From this perspective, we conducted a double-masked, crossover, randomized clinical trial to assess the efficacy of spectacle lenses with rings of contiguous slightly aspherical lenslets.

We followed 100 children randomized into two groups of 50. The two groups were well matched for the main covariate parameters, such as age, spherical equivalent refractive error, and AL (0.49 < p < 0.94), minimizing their effects on the results of the study.

In this study, we adopted a one-year crossoverdesign that is not very common in myopia research. We believe that this approach has merit, particularly for completely novel interventions whose myopia control effect is difficult to infer from previous studies. Unlike regular clinical trial design, this crossoverdesign may provide a within-subject treatment comparison with little to no influence of genetics and other subject-specific factors. However, it must be noted that these analyses should be interpreted with caution because they may be biased by possible carry-over effects or difficulty with subject masking.

We also opted to have a shorter interval (maximum of 3 months) between the study visits; that is, a maximum of 3 months versus the more standard 6 months. This decision was motivated by the interest in evaluating the myopia control effect of SAL lenses at finer temporal resolution. Although cycloplegic SER and AL are only taken at baseline, and at the 6- and 12-month visits to minimize cycloplegia, we believe that these data will provide valid evidence for the effect of myopia control.Moreover, AL without cycloplegia will be taken at the 3-, 5-, and 9-month visits, and these data will be informative. First, the AL is considered animportant index to evaluate myopic progression [34, 35]. Second, previous research has indicated that (lack of) cycloplegia has no significant effect on AL [36]. In addition, 3-month visits may allow better compliance through parent and child engagement and, more often, equipment checks.

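### Allocation is covariate-adaptive but the 6-month lens comparison is an unadjusted t test, so its standard error is too large and the test conservative if the covariates predict progression

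*Protocol article*

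**What the plan says.** Randomization and masking gives the allocation method: "All subjects were assigned into the two groups (described in the Study Design section) at a 1:1 ratio using covariate-adaptive randomization".

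Main outcome measures names two outcomes: "There are two main outcome measures: the axial length (AL) and the spherical equivalent (SER) of cycloplegic autorefraction". Prospective data analyses takes the change from baseline in each and fixes the test: "Myopia progression and axial elongation will be compared between the SAL lenses and the single vision lenses using independent-samplet test". No covariate is attached to that test.

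The same section plans one model with covariates: "A multivariate regression model will be used to evaluate the relationships between variables such as age, gender, baseline myopia, parental myopia, NPC and phoria level", each related to progression. Lens type is not among the variables listed, and the model is not described as estimating or testing the lens effect.

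The Discussion reports on balance: "The two groups were well matched for the main covariate parameters, such as age, spherical equivalent refractive error, and AL". It adds that this matching limits the influence of those variables on the results.

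**The concern.** Covariate-adaptive allocation is chosen to keep the groups alike on variables thought to predict outcome. The ordinary two-sample t test computes its standard error as if those variables could differ between groups by chance alone. When allocation has suppressed that chance imbalance and the variables do predict progression, the true sampling variation of the difference in means is smaller than the reported standard error. The test then rejects a true null less often than 5%, and the interval is wider than the data warrant.

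The planned regression does not repair this, because it is not the lens comparison. Nor does baseline balance. Balance protects the point estimate from confounding, but it leaves covariate-explained variance in the error term of the t test.

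What is at stake is the width of the interval for the lens effect and some power. For a new lens design, the size of the effect is a main product of the trial.

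**Working it through.** **Inputs.** From Study participants: "80% power to detect a minimum difference of 0.27 D with an SD of 0.37 D at 6 months", a 5% significance level (taken as two-sided) and 42 per group before drop-out. The share of variance in 6-month progression explained by the allocation covariates, R², is not given anywhere. It is an assumption, shown at 0.10, 0.20 and 0.30.

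**The plan's own figure.** n per group = 2 × 0.37² × (1.960 + 0.842)² / 0.27² = 29.5, so 30 (31 with the t distribution), not 42. With 42 per group, the power is Φ(0.27/0.0807 − 1.960) = Φ(1.384) = 91.7% (91.1% with the t distribution). The mismatch is a separate matter. It enters here only because it shows that the SER comparison has power to spare.

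**Unadjusted interval.** SE = 0.37 × √(2/42) = 0.0807 D; half-width = 1.96 × 0.0807 = 0.158 D.

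**Adjusted interval.** Removing the explained variance multiplies the SE by √(1 − R²).

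**Type I error, limiting case.** Under perfect balance the unadjusted z statistic has standard deviation √(1 − R²) under the null, so the rejection rate is 2 × [1 − Φ(1.96/√(1 − R²))].

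**Power at 0.27 D, limiting case.** Unadjusted: Φ((0.27 − 0.158)/(0.0807 × √(1 − R²))). Adjusted: Φ(0.27/(0.0807 × √(1 − R²)) − 1.96).

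**Simulation.** Minimization of 84 children on three two-level factors with a biased coin of 0.8; two factors were continuous covariates split at zero, and the adjusted model used their continuous values. There were 4,000 trials under the null and 2,000 at 0.27 D for each R².

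| Assumed R² | 0.10 | 0.20 | 0.30 |
|---|---|---|---|
| √(1 − R²) | 0.949 | 0.894 | 0.837 |
| Adjusted half-width (D), against 0.158 | 0.150 | 0.142 | 0.132 |
| Type I error, unadjusted, perfect balance | 3.9% | 2.8% | 1.9% |
| Type I error, unadjusted, simulated | 4.6% | 3.7% | 3.0% |
| Type I error, adjusted, simulated | 5.1% | 5.2% | 5.2% |
| Power, unadjusted / adjusted, perfect balance | 92.8% / 94.1% | 93.9% / 96.2% | 95.1% / 97.9% |
| Power, unadjusted / adjusted, simulated | 91.8% / 93.2% | 91.8% / 94.8% | 94.2% / 98.2% |

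The Monte Carlo error on a 5% rate with 4,000 trials is √(0.05 × 0.95/4000) = 0.3 percentage points. At R² = 0 both tests returned 4.3%, so the simulated rates should be read to within about 0.7 points.

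**Which column of results is realistic.** Perfect balance is a limit. The article's own baseline table shows sex split 27/23 in both groups and age nearly equal (p = 0.94), but axial length differs by 24.89 − 24.79 = 0.10 mm with p = 0.49. Simple randomization would produce a larger difference about half the time. The simulated figures are therefore the better guide.

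**Axial length.** The documents give no SD for change in axial length, so no half-width in mm can be computed. The proportional narrowing, about 5%, 11% or 16%, applies to either outcome at the same R².

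**The case against.** The strongest reply is that the harm is small, runs in the safe direction and is of unknown size. R² rests on no figure in the documents, and at R² = 0 there is no loss. At R² = 0.10 the simulated test size is only 0.4 points below 5%. The gain in half-width is 0.008 to 0.026 D, and SER power is already about 91% against a target of 80%. All of this stands, and it makes the point one of efficiency.

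It is also fair that the article does not limit the t test to the first period. If both periods were pooled by lens, each child who completes would contribute to both lenses, and child-level covariates would balance whatever the allocation method. The pairing and period effects ignored by such a test would be a different issue. This point therefore covers the first-period comparison only. A reader might infer that the crossover analysis needs the same covariates. With complete data it does not, because child-level main effects cancel in a within-child contrast.

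Three further readings are tempting, and the text does not support them.

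- That the allocation description contradicts itself, because it also says "A scheduled randomization was generated and children were randomly assigned by Study Manager". Nothing states that the list was drawn up before enrolment, and an adaptive procedure also yields a list of assignments to conceal. The wording is awkward, no more.
- That failing to name the balancing factors is a defect. An article may leave that to the full protocol or analysis plan. Age, SER and axial length are called main covariates in the Discussion, but they are not said to be the allocation factors.
- That the Discussion rejects adjustment on the ground that the groups are matched. Its remark is a reasonable one about confounding and says nothing about adjustment.

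**Conclusion.** The mismatch is in the text: allocation is covariate-adaptive, and the stated lens comparison uses no covariates. For the 6-month between-group comparison, the unadjusted test overstates the standard error whenever the balanced covariates predict progression.

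A reader might take a test that is not at its nominal 5% to be invalid. It is not: the error rate lies below 5% and the difference in means is unbiased. Nor is the point estimate itself much less precise, since balance has already done most of that work; the fault is mainly in the reported standard error.

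The size depends wholly on an assumed R², and the limiting type I errors should be read as the worst case rather than the expected one. The half-widths and power also assume 42 per group and the plan's SD of 0.37 D. The practical effect on SER is modest. For axial length no power margin is shown, so the cost there cannot be judged. The change is worth making because it is nearly free.

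**What to change.** In Prospective data analyses, replace the unadjusted t test for the 6-month comparison with an ANCOVA on change in SER and another on change in axial length. Each should include lens group, age, sex, the corresponding baseline value (SER or axial length) and any other factor used in the allocation algorithm. Report the adjusted lens difference with its 95% confidence interval as the result of that comparison.

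The cost is analysis wording and a few degrees of freedom: with 84 children and three covariates, the residual degrees of freedom go from 82 to 79. Age, sex, SER and axial length are already in the baseline tables, and any other allocation factor must have been recorded in order to allocate. If the covariates turn out to predict nothing, the loss is slight: simulated power at R² = 0 was 90.9% adjusted against 91.6% unadjusted.

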### Test lenses

The treatment lens is a polycarbonate single vision spectacle lens with a spherical front surface with 11 concentric rings formed by contiguous slightly aspherical lenslets.

The control lens is a standard polycarbonate single vision lens.

### Main outcome measures

There are two main outcome measures: the axial length (AL) and the spherical equivalent (SER) of cycloplegic autorefraction. The AL is measured using an optical low-coherence reflectometry device (Lenstar LS900; Haag-Streit, Koeniz, Switzerland). Five measurements were taken, and the average value per eye was used for data analysis. The refraction is measured by closed-field autorefractors (Topcon KR-800 and Topcon 8900). The measurement was taken ten times on each eye and the mode of the sphere, cylinder, and axis per eye is recorded for data analysis. The SER is calculated as sphere + 0.5 × cylinder. The SER is taken only at baseline, the fifth visit and the last visit to minimize cycloplegia during the study.

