### Study visits and procedures

The procedures performed at each visit are summarized in Table 1.

**Table 1 Tab1:** Visit schedule for the study. V1 to V7 represent visits 1 through 7. AL Axial length, *CT* Corneal thickness, *ACD* Anterior chamber depth, *LT* Lens thickness, *DCVA* Distance-corrected visual acuity

Visit schedule	V1	V2	V3	V4	V5	V6	V7
Informed consent	X						
Eye examination	X						
Inclusion and exclusion criteria	X						
Study frame choice	X						
Monocular pupillary distance and fitting measurements	X			X			
Washout spectacles delivery	X						
Study spectacles delivery		X			X		
AL, CT, ACD and LT measurements	X	X	X	X	X	X	X
Cycloplegic autorefraction	X				X		X
Non-cycloplegic subjective refraction	X			X			
DCVA	X	X	X	X	X	X	X

During the recruitment and baseline visit (V1), we first performed a full ocular examination, including presenting visual acuity, objective and subjective refraction, anterior segment and fundus inspection, and binocular vision status (near and far phoria, near point of convergence (NPC), Worth 4-dot test), followed by acquisition of the primary outcome measures (cycloplegic SER and AL) and all secondary outcome measures (DCVA, AL, CT, ACD, and LT). The subjects chose their frame, and the same frame was used for SAL and control single vision lenses, i.e., before and aftercrossover. At the end of the baseline visit, the subjects are dispensed with washout single vision lenses corresponding to the prescription for their first study equipment.

The main follow-up visits included the 6-month crossovervisit (V5) and the final 12-month visit (V7) with all primary outcome measures, including the questionnaires.

The additional study visits comprise the dispensing visit (approximately one month after the baseline, V2), 3-month (V3), 5-month (V4), and 9-month visits (V6) with only noncycloplegicAL and secondary outcome measures. In addition, at the 5-month visit, we acquired noncycloplegicsubjective refraction as a basis for the prescription for the study equipment worn during the second phase of the study (i.e., aftercrossover). Before ordering a new prescription, trial frame was used to confirm comfort of each participant.

Between one and three days after the dispensing visit and 6-month visit, we administered the compliance and adaptation questionnaire over the phone.

During all study visits, the study equipment was adjusted, and subjects were instructed to wear it at least 7 h per day.

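### The named t test on 6-month change in axial length drops children who leave before V5, although their axial length is measured at V3 and V4 and a repeated-measures model would use it

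*Protocol article*

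**What the plan says.** - Main outcome measures: "There are two main outcome measures: the axial length (AL) and the spherical equivalent (SER) of cycloplegic autorefraction". For refraction, "The SER is taken only at baseline, the fifth visit and the last visit to minimize cycloplegia during the study".
- Study visits and procedures: Table 1 marks AL at all of V1 to V7. The text describes the interim visits as "3-month (V3), 5-month (V4), and 9-month visits (V6) with only noncycloplegicAL and secondary outcome measures". At V4 a non-cycloplegic subjective refraction is also taken, "as a basis for the prescription for the study equipment worn during the second phase of the study".
- Prospective data analyses: the analysis variable is the change in each main outcome, and these changes "between the follow-up and baseline data will be used to evaluate myopia progression". The test named for the lens comparison is the independent-sample t test: "Myopia progression and axial elongation will be compared between the SAL lenses and the single vision lenses".
- Study participants: the design aims to detect 0.27 D with an SD of 0.37 D at 6 months. "Allowing a maximum drop-out rate of 15%, the number to be recruited for each group was estimated to be 50".
- Discussion: "AL without cycloplegia will be taken at the 3-, 5-, and 9-month visits, and these data will be informative".

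**The concern.** The schedule and the test do not fit together well for AL. AL is collected at V2, V3, V4 and V5 in the first period, but a t test on the 6-month change uses only children who have a V5 value. A child who leaves in month 4 or month 5 has one or two on-lens AL readings, and none of them reaches the 6-month lens comparison. For cycloplegic refraction the same child has no value after V1.

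The extra recruitment restores the number of children, not their mix. If the children who leave single vision lenses are those whose eyes grow fastest, the remaining control mean is too favourable and the lens effect is understated. If the slenslet-lens (SAL) arm loses children for some other reason, the distortion may take another form. For AL, the readings that could correct much of this are already being taken.

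**Working it through.** **Inputs from the article.** Difference 0.27 D, SD 0.37 D, 80% power, 5% level (taken as two-sided), 42 per group, 15% drop-out, 50 recruited per group (Study participants). AL at V1 to V7, cycloplegic refraction at V1, V5 and V7 (Table 1).

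**1. The plan's own figures.** The drop-out step reproduces: 42 / 0.85 = 49.4, rounded up to 50. The 42 does not follow from the stated inputs: 2 × (1.960 + 0.842)² × (0.37 / 0.27)² = 29.5, so 30 per group (31 by the exact t test). That is a separate matter and errs on the safe side. With 42 completers per group, power for 0.27 D is about 91%. Loss of numbers is therefore not the issue here; the question is bias.

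**2. Refraction, worst case.** Suppose the fastest 15% leave one arm only. The mean of the remaining 85% of a normal distribution shifts by φ(1.036) / 0.85 = 0.2332 / 0.85 = 0.274 SD. In dioptres this is 0.274 × 0.37 = 0.101 D, or 0.101 / 0.27 = 38% of the target. The observed difference would be about 0.17 D.

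**3. Refraction, graded cases.** The assumptions here are not in the article: mean 6-month change −0.45 D on single vision and −0.18 D on SAL, 15% loss overall, and loss more likely with faster progression.

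| Log-odds of leaving per dioptre | Loss, single vision / SAL | Complete-case difference |
|---|---|---|
| 0 | 15% / 15% | 0.27 D |
| 1 | 17% / 13% | 0.27 D |
| 2 | 18% / 12% | 0.26 D |
| 4 | 20% / 10% | 0.23 D |
| 8 | 22% / 8% | 0.20 D |

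The bias runs from about 0 to −0.07 D. If both arms lose the same share of their fastest progressors, the mean difference does not move.

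**4. Axial length.** The assumptions, again not in the article, are: 6-month growth 0.18 mm on single vision and 0.10 mm on SAL (true difference 0.080 mm), SD 0.10 mm, measurement error 0.03 mm, 50 per arm. Eight single vision children leave after V4, before V5. Leaving depends on growth seen at V4, fully or with a correlation of 0.5 or 0.3.

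| Dependence of leaving on V4 growth | Complete-case difference | Bias | Repeated-measures estimate |
|---|---|---|---|
| Full | 0.053 mm | −0.027 mm (34%) | 0.080 mm |
| 0.5 | 0.067 mm | −0.013 mm (16%) | 0.080 mm |
| 0.3 | 0.072 mm | −0.008 mm (10%) | 0.080 mm |

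Hand check: removing the top 8 / 50 = 16% shifts the mean by φ(0.994) / 0.84 = 0.2433 / 0.84 = 0.290 SD, and 0.290 × 0.10 = 0.029 mm if leaving were decided by true growth. Times 0.5 and 0.3 this gives 0.014 and 0.009 mm, in line with the table.

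The full recovery in the last column follows from the set-up: leaving depends on AL that was observed, which is what missing at random means.

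**The case against.** - **A reader might infer that an early leaver adds nothing to the primary result.** The article does not support that. AL is a main outcome, and a child who attends V3 and V4 has on-lens AL at 3 and 5 months. The data analysis section does not confine follow-up to V5 or V7, so separate comparisons at V3, V4 and V6 would fit its wording. This stands. But a t test at V3 or V4 does not carry the leaver's data into the 6-month estimate.
- **A reader might infer that the lens effect will be biased.** The article gives no evidence of loss related to progression. The trial is described as double-masked, and every child is due to wear the SAL lens in one period. The Discussion reports that none of the children with early blur or dizziness discontinued for an adaptation problem. On the other hand, it concedes possible difficulty with subject masking and notes that no new equipment was dispensed at V3 and V6 although myopia may have progressed. The bias is a risk, not a fact, and in the cases computed it runs towards no effect.
- **A reader might treat the three-visit refraction schedule as a fault.** It has a stated reason, to limit cycloplegia in children, and non-cycloplegic AL fills the gaps. It is not an error.
- **A reader might infer that the trial has no plan for missing data, exit visits or follow-up after lens wear stops.** The article is condensed, and such rules may sit in a full protocol or analysis plan that is not shown. Their absence is not part of this point.

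What remains is narrower: the article names a test for AL that makes poor use of a schedule it sets out itself.

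**Conclusion.** The point holds for the choice of AL analysis and is conditional in its size. A child lost between V3 and V5 leaves the 6-month AL t test despite having measured on-lens AL, and also lacks any post-baseline cycloplegic refraction. If loss depends on progression and differs by arm, the AL difference is understated by about 0.01 to 0.03 mm of 0.08 mm when 8 of 50 single vision children leave, and the refraction difference by up to 0.10 D of 0.27 D at the extreme. The AL growth figures, the refraction means in the graded cases and all the leaving patterns are assumptions; the 0.27 D, 0.37 D and 15% are the article's own. Bias is nil if loss is unrelated to progression or takes the same share of fast progressors from both arms.

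**What to change.** In Prospective data analyses, replace the independent-sample t test for AL with a likelihood-based repeated-measures model on all AL visits in each period: V2 to V5, and V5 to V7 where second-period data are used. Include lens, visit and lens-by-visit terms, and take the 6-month lens difference from the model as the estimate, so that leavers contribute the AL that was measured.

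The cost is slightly more analysis work; no visit or measurement is added. The model rests on a missing-at-random assumption. It does nothing for the refraction outcome and does not help with a child who leaves before V3, so both limits should be stated with the result.
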